### Procedure

1.3

The SES NXT trial is designed as a randomized controlled, parallel-group, superiority trial that compares a waitlist control group with the digital SES NXT intervention program. The primary endpoint is 12 weeks post-baseline (T3). Fig. 1 presents the CONSORT diagram. We elect to collect data from participants at T1, T2, and T3, for the following reasons: 1) we want to see whether there are short-term positive effects of using the intervention, and we believe that 4 weeks (T2) is sufficient time for participants to access and engage with the intervention, 2) in a previous study of an adult divorce intervention, we found that improvements were largest at the 12-week (T3) time point and plateaued at subsequent time points (i.e., Hald et al., 2020a), and 3) we received push-back from grant reviewers, indicating that longer follow-up times were ethically unacceptable, as they would delay access to the intervention for those in the control group.

**Fig. 1 f0005:**
[figure not shown]
CONSORT diagram.

Families are recruited through Danish municipalities and the Agency of Family Law; municipal officials distribute informational fliers through the school/daycare online parent portals every 3 months or refer the families directly to the sign-up website. Physical posters and postcards are hung in high-foot traffic areas within the schools and daycares. Moreover, caseworkers can refer clients to the study by sharing the informational fliers. Interested parents access a website that provides information about the study and the study sign-up sheet. Specifically, they are informed about the structure of the study (surveys at baseline, 4 and 12 weeks, the use of a wait-list control group) and the associated incentive structure (movie tickets for survey and module completion; see below), as well as about efforts taken to protect their data and their rights as a participant (e.g., voluntary participation, can withdraw from the study at any time). Moreover, they are provided with contact information for the study responsible, in case of any questions or issues, and contact information for technical support, in case of issues accessing the intervention.

In the sign-up form, they are asked to indicate whether they are the custodial parent of one or more children aged 3–17 years and to provide the name, age, and contact information for each child. Parents provide their own e-mail and/or phone number, or that of their children. Consent is collected at the end of the sign-up form, with a check box. Custodial parents consent to study participation on behalf of themselves and their children; only the parents who sign the children up for the project provide consent. Given the online nature of the study, we are unable to obtain child assent. However, we advise the parents to talk to their child about study participation and use of the digital intervention.

Families are randomized to either the intervention or the wait-list control group. Randomization is performed electronically, with a random number generator, and randomization occurs at the family level, such that parents and children are randomized to the same group, at a 1:1 allocation ratio. Participants (i.e., parents and children aged 11–17) are sent e-mails and/or text messages containing links to the online T1 survey, and upon completion of the T1 survey, they are informed of their group allocation. Intervention group participants receive access to the intervention immediately. Access to SES NXT is provided to the specific child, for whom the T1 survey is completed; that is, if a mother completes a survey for “Child 1”, but not “Child 2”, then only “Child 1” receives access to SES NXT. User accounts are automatically generated for each child that is signed up.

After signing up, parents receive an e-mail and/or text message with a link to a short survey about themselves. Parents also receive individual links via e-mail and/or text message to questionnaires for each child aged 3–10 years. Youths aged 11–17 years receive links via e-mail and/or text message to surveys for them to complete on their own; in cases, where children do not have their own e-mail address or mobile phone number, parents may list theirs and share the survey with the youth. Upon completion of the baseline (T1) questionnaire, participants receive follow-up questionnaires 4 weeks (T2) and 12 weeks post-baseline (T3). Even if participants do not complete the T2 survey they still receive the T3 survey. Table 1 provides an overview of the scales completed at each timepoint. Participants in the control group receive access to SES NXT after T3, regardless of whether they respond to the T2 and T3 surveys.

**Table 1 t0005:** Overview of measurement.

	Parent	Age 3	Age 4–10	Age 11–17
	Self-report	Parent report	Parent report	Self-report
Socio-demographic questions and relationship/divorce questions	T1			
Divorce conflict (Hald et al., 2020b)	T1, T2, T3			
Depression symptoms (PHQ-2; Kroenke et al., 2003)	T1, T2, T3			
Anxiety symptoms (GAD-2; Kroenke et al., 2007)	T1, T2, T3			
Strength and Difficulties Questionnaire (Goodman et al., 1998)		T1, T2, T3	T1, T2, T3	T1, T2, T3
Physical health: Somatization (SDQ, item 3), body dissatisfaction, sleep quality		T1, T2, T3	T1, T2, T3	T1, T2, T3
School and daycare attendance (Heyne et al., 2020)		T1, T2, T3	T1, T2, T3	T1, T2, T3
The Quality of My Life Questionnaire (Gong et al., 2007)				T1, T2, T3
Perceptions of parental conflict (Hald et al., 2020b)				T1, T2, T3
Platform focus: Communicating needs, setting boundaries, and connecting with adults			T1, T2, T3 (age 6–10)	T1, T2, T3
Support services		T1	T1	T1

Note. T1 = baseline, T2 = follow-up at 4 weeks post-baseline, T3 = follow-up at 12 weeks post-baseline. The primary and secondary hypotheses specify the child-related questions as outcomes; parent self-report is used as covariates.

To optimize participant retention, we implement two strategies: 1) All participants receive reminder e-mails and/or text messages to complete the questionnaires two and five days after the survey link is sent out. 2) We provide two movie tickets (value 180 DKK/24 EUR) for active participation. Specifically, participants in the control group earn one movie ticket for completing two surveys and one additional movie ticket for completing all three surveys. Participants in the intervention group earn one movie ticket for completing two surveys and three SES NXT modules. They can earn an additional movie ticket for completing all three surveys and three modules on the intervention platform. The tickets are earned individually, for each child.

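### Families are randomised as a unit but the arm is disclosed on T1 completion, child by child, so later siblings can complete T1 with the arm already known

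*Protocol article*

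**What the plan says.** All of the following is in section 1.3 (Procedure) of the protocol article unless noted.

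- Unit of randomisation: "randomization occurs at the family level, such that parents and children are randomized to the same group, at a 1:1 allocation ratio".
- T1 collection, younger children: "Parents also receive individual links via e-mail and/or text message to questionnaires for each child aged 3–10 years".
- T1 collection, older children: "Youths aged 11–17 years receive links via e-mail and/or text message to surveys for them to complete on their own". A parent may give their own contact details and pass the survey on.
- Disclosure: "upon completion of the T1 survey, they are informed of their group allocation".
- Access: "Intervention group participants receive access to the intervention immediately", and "Access to SES NXT is provided to the specific child, for whom the T1 survey is completed". The article's own example is a mother who completes T1 for one child but not for another; only the first child gets access.
- Follow-up: the T2 and T3 questionnaires are sent once T1 has been completed.
- Sign-up: the parent lists every child and consents for all of them before any T1 survey.
- Analysis (section 1.6): the outcome's baseline score is a listed covariate, and attrition is studied by comparing those who completed only T1 with those who stayed on after T1.

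The article does not hold disclosure back until all of a family's T1 surveys are in, does not close T1 entry at disclosure, and does not treat children by whether their T1 came before or after it.

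**The concern.** With family-level randomisation, learning one child's arm means learning every sibling's arm. The clearest case is a parent with two children aged 3–10. The parent finishes one survey, learns the arm, and then decides whether and how to complete the next. For that second child, T1 is the step that opens follow-up in both arms and access in the intervention arm.

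Two things are at stake. First, which siblings enter the followed-up sample can depend on arm, so the randomised comparison is no longer protected for those children. Second, their T1 score, meant as a pre-allocation covariate, can be reported in the knowledge of the arm. The primary outcomes are parent- or self-reported SDQ scores, which are open to expectation. A larger sample removes neither problem, and an attrition analysis that begins with T1 completers cannot see a registered sibling who never completed T1.

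**Working it through.** **Order of events.** Put side by side, the section 1.3 statements give: (1) one arm per family; (2) several T1 surveys per family; (3) disclosure and access on T1 completion; (4) access released to one sibling while another's T1 is outstanding; (5) follow-up dependent on T1. Reminders two and five days after the link is sent show that spread-out completion is foreseen. From (1) to (5), a later sibling's T1 can follow disclosure. This needs no numbers.

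**The plan's own figures.** Section 1.1 gives a planned difference of 0.40 points on SDQ-Emotional, 90% power, alpha 0.05 and roughly 700 clusters. The SD, intra-family correlation and children per family are not given, so 700 cannot be confirmed or refuted. With one child per family and a two-sided test, SD 1.63 gives n per arm = 2 × (1.960 + 1.282)² × 1.63² / 0.40² ≈ 349, or 698 in total. With 1.5 to 2 children per family and a correlation of 0 to 0.5, 700 clusters correspond to an SD of about 1.8 to 2.3. The point does not depend on this; 0.40 serves only as a yardstick.

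**Illustration A: unequal sibling entry (all inputs assumed).** Let 45% of families have a second eligible child, with sibling T1 completion of 80% in the intervention arm and 60% in control.
- Children per family: 1 + 0.45 × 0.80 = 1.36 and 1 + 0.45 × 0.60 = 1.27.
- Excess share in the intervention arm: (1.36 − 1.27) / 1.36 = 6.6%.
- If the extra children differ by 0.5 to 1.0 points, the shift is 0.066 × 0.5 = 0.033 to 0.066 × 1.0 = 0.066, which is 8% to 17% of 0.40.
- At 90% power the standard error is about 0.40 / 3.24 = 0.12, so the shift is about a quarter to a half of a standard error. Two-sided type I error would move from 5% to about 6–8%.

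**Illustration B: simulation with no true effect (all inputs assumed).** SD 2.2, intra-family correlation 0.3, half of families with a second child. Entry in the intervention arm rises with severity; entry in control does not.

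| Nominal sibling entry, intervention / control | Severity slope in intervention arm (logit per SD) | Intervention minus control |
|---|---|---|
| 90% / 90% | 0 | −0.004 |
| 90% / 60% | 0.5 | 0.044 |
| 80% / 50% | 0.5 | 0.058 |
| 70% / 50% | 0.5 | 0.074 |
| 80% / 50% | 1.0 | 0.126 |

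The non-null rows are 11% to 32% of 0.40. With this assumed selection the sign runs against H1.

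**Baseline route (assumed).** If 25% of intervention-arm children have T1 scores shifted by 0.3 points and the T1-to-T3 slope is 0.6, the adjusted difference moves by 0.6 × 0.3 × 0.25 = 0.045. Over-reporting at T1 in the intervention arm would move it towards H1, under-reporting away from it. This can offset the selection effect or add to it.

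**Reach of a time-stamp filter.** Under the inputs of A, if every second child's T1 follows disclosure, later siblings are (0.36 + 0.27) / (1.36 + 1.27) = 0.63 / 2.63 = 24% of all children.

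**The case against.** - **The wording permits late entry but does not show it.** The article does not say whether the message fires after each link or after a participant's whole set of T1 surveys, and such platform logic may sit in the full protocol. This stands in part: a reader might infer that later siblings do enter unblinded, but the text supports only that they can. Child-by-child release remains the natural reading, because access is immediate, is given per child, and itself reveals the arm.
- **Recruitment is partly protected.** Every child is named and consented at sign-up, before disclosure. This stands. A reader might infer that children are identified after allocation is known; they are not. Only T1 completion is exposed.
- **Intention-to-treat with multiple imputation could cover missing siblings.** A reader might infer that children without T1 are excluded, but section 1.6 does not say so. It does not say that they are included either. Imputing a child with neither T1 nor follow-up data would carry little information.
- **Incentives do not all pull one way.** Completing T1 gives an intervention child immediate access. Movie tickets are earned per child, and control children earn them for surveys alone, whereas intervention children must also complete three modules. This stands: even the sign of a difference in sibling entry is uncertain.
- **Baseline adjustment absorbs some selection.** It would, where T1 is reported blind. For later siblings the T1 score can itself be arm-aware, so the protection is incomplete.
- **The figures are assumed and unadjusted.** This stands in full.

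**Conclusion.** The sequence in section 1.3 leaves a gap. In multi-child families with staggered T1 completion, later siblings can complete T1 with the family's arm known, so their entry and their baseline score can depend on arm, and the planned attrition analysis would not reveal it. First-completed children and single-child families are not affected by this route.

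The illustrations give roughly 0.03 to 0.13 points unadjusted, or 8% to 32% of the planned 0.40, and about zero when entry is equal and unrelated to severity. They rest wholly on assumed entry rates, family sizes and severity differences, so size and direction in this trial cannot be derived from the article. A reader might infer a bias in favour of the intervention; the article does not support that, since the plausible mechanisms run in both directions. The point is a should-fix.

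**What to change.** **Procedure.** Withhold the allocation message and platform access until all T1 surveys for the family's registered children are completed, or until a short fixed window after the links go out has closed. This is one rule in the automated messaging and costs some families a few days' delay.

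**Families already enrolled.** Enrolment was to close by 31 August 2024 at the latest, so this part may be all that is still open. Before analysis, use survey time stamps to:

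1. report T1 completion per registered child, by arm;
2. pre-specify a sensitivity analysis limited to children whose T1 preceded the family's first disclosure, whether by message or by access.

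The cost is a time-stamp filter and a possibly substantial loss of sibling records in that set: about 24% of children in the extreme case worked above, leaving about one child per family. For that reason it belongs as a sensitivity analysis and should not replace the main analysis set.

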### Intervention description

1.4

SES NXT is a digital intervention for children and youth aged 3–17 years, who experience parental relationship dissolution. The intervention includes various elements such as text, videos, motion graphics, and voice-overs, and highly interactional content such as digital activities and exercises. SES NXT is designed to be adaptive to the youth's age. The intervention has four age categories correspond to the Danish daycare and school system, with 3–5-year-olds attending daycare and kindergarten, ages 6–8 years representing pre-school and start of primary education, ages 9–12 years representing primary education and start of lower secondary education, and ages 13–17 years representing lower secondary education and start of secondary education (e.g., high school). The format of the intervention was adapted to reflect the cognitive, social, emotional, and digital competencies of each of those age groups. Specifically, the intervention for children aged 3–5 consists of videos with speak that the parent and child can watch together and contain dialogue questions for the parent to initiate conversations with the child about the theme in question. Youth ages 6–8 are able to manage a digital tool on their own (with less parental guidance), but may not be able to read; therefore, the intervention consists of videos with speak and some short texts at a low reading level. For youth aged 9–12 and 13–17, the intervention consists of videos, texts, and interactive content, reflecting their greater reading level and digital competencies. However, the interventions for the two age groups differ with respect to their level of abstraction. Moreover, videos that contain other children (i.e., “peers”) present children in the same age range as the participants (e.g., 9–12-year-olds watch videos of other 9–12-year-olds).

The intervention addresses key factors associated with adjustment to parental relationship dissolution, such as perceived support (Sorek, 2020), coping skills (O'Hara et al., 2019; Sandler et al., 2000), child-parent relations and communication (Gunter Castleton, 2020; Kunz, 2001; O'Hara et al., 2019; Wal et al., 2021), and the interpretation and meaning made of the relationship dissolution (e.g., loss, gain, change, healing) (Brand et al., 2017; Venta and Walker, 2021). Table 2 provides an overview of the modules included in the intervention for each age group. Each module comprises a theme identified in the literature as central to youths experiencing parental relationship dissolution (e.g., living in two homes, bonus families, and parental conflict). Most of the content in the intervention is covered across the age groups, though in age-appropriate ways. An example of this is the module(s) concerning emotions (i.e., “Feelings” for 3–5-year-olds and 6–8-year-olds and “Understand your feelings” for 9–12-year-olds and 13–17-year-olds), which covers the various emotions that one might experience in response to a parental relationship dissolution. Different emotions are described: sadness and longing, guilt, joy, fear and insecurity, anger. For the two older age groups, the text for sadness and longing is: “Sadness and longing are the best! Because it shows you that someone or something means a lot to you. In other words, it's a sign of love. But... isn't it bad to be sad? No, actually not. It can be tough and hard, but if you were never sad, it would actually be a little sad.” The texts are (often) the same for the 9–12- and 13–17-year-olds and they are introduced to an understanding of emotions as good, even though they can be difficult to experience.

**Table 2 t0010:** Intervention content overview, by age group in the intervention.

Theme	Age 3–5	Age 6–8	Age 9–12	Age 13–17
*Family Constellations*				
My Family	X			
The Bonus Family		X	X	X
*Practical Matters*				
Changeover Day	X			
Living in Two Places		X	X	X
Packing Your Bag		X	X	X
*Emotional Aspects of Parental Divorce*				
Missing Someone Means You Care	X			
Feelings	X	X		
Understand Your Feelings			X	X
When It has Just Happened		X	X	X
Tell Your Story			X	X
*Agency*				
Find an Important Adult		X	X	X
Learn To Say Yes and No		X	X	X
My Parents Are Not Getting Along		X	X	X
My Rights			X	X

Building on the example, the theme of longing is also addressed for the 3–8-year-olds. Here, the text is: “Everyone sometimes misses someone they care about. Both children and adults. To miss means thinking about someone who isn't there. Someone you care about. Maybe you can feel it in your stomach? Maybe you become a little sad? It could also be that you're looking forward to seeing the person you miss. That's totally okay.” Children in the 3–5 and 6–8 age groups are introduced to the concept of “longing”, a common emotional response, and are made to understand that they can feel this way when their parents have separated. In essence, for these modules, the intervention seeks to help the younger children to mentalize various feelings, while the older youth are challenged to understand emotions at a higher level of abstraction, as they must recognize that what feels hard may also be important.

The guiding principles interwoven into the digital modules are: 1) *The mind is social* (Tomm, 1984): Human behavior, emotions, and cognitions are situated in a social context. 2) *Re-connection* (Perry, 2013): When children experience significant life changes, connections with existing values, hopes, or dreams may change. The child is guided to re-connect with these in the same or in an altered form, depending on new life circumstances. 3) *Agency* (White, 2008): The experience of and belief in the ability to influence the world around oneself and not only be the passive recipient of what happens around oneself. 4) *Appropriate disturbance* (Schjødt and Ekeland, 2008): An ‘appropriate disturbance’ typically refers to a disruption or challenge that is constructive and suitable within a specific context. This type of disturbance is designed to evoke thought, encourage growth, or create necessary change without causing harm or undue stress. 5) *Normalization* (White, 2008): When youths face parental relationship dissolution, they may feel they have failed or done something wrong, and think they are alone in these difficult emotions. Normalizing these feelings by showing them they are not alone can make them less distressing and intrusive. 6) *Mentalization* (Aasen and Fonagy, 2021): The ability to understand mental states of oneself and other.

The intervention can be accessed at any time during the trial by logging into the intervention website from a mobile smartphone, tablet, or computer. Given that divorce is a heterogeneous process, and the experience of divorce is different for each individual, participants choose the modules that are most relevant to them. The modules can be completed in any order, as little or much as desired, and repeated as needed.

### Measures

1.5

All questions are completed at baseline (T1), 4 weeks post-baseline (T2), and 12 weeks post-baseline (T3); parents complete questionnaires on behalf of their children aged 3–10, while youth aged 11–17 complete the questionnaires themselves. Table 1 provides an overview of the measurements in the study.

The Strength and Difficulty Questionnaire (SDQ; Goodman, 1997; Goodman et al., 1998) is used to measure emotional, behavioral, and social difficulties. The SDQ consists of a self-report version (from age 11) and proxy report version for parents, both including 25 items rated on a 3-point scale (i.e., 0 = “not true”, 1 = “somewhat true”, and 2 = “certainly true”). The items are divided into five 5-item subscales that generate a score for: 1) Emotional problems, 2) Conduct problems, 3) Hyperactivity/inattention, 4) Peer relationships problem, and 5) Prosocial behavior. Scores for each of the subscales can range from 0 to 10. A total SDQ difficulty score is calculated by summing up the difficulties across the four problem areas (not including prosocial behavior); scores range from 0 to 40, with higher scores indicating more mental well-being related difficulties. The extended version of the SDQ contains an impact scale that asks questions about child distress and interference of problems with home life, friendships, classroom learning, and leisure activities. The SDQ impact scale consists of 5 items, rated on a 4-point scale (i.e., 0 = “not at all”, 1 = “only a little”, 2 = “a medium amount”, and 3 = “a great deal”). The items are summed, and the resultant score can range from 0 to 10, with higher scores indicating greater impact of problems on daily life. The SDQ is a well-established and widely used measure that has shown good psychometric properties in a Danish sample (Arnfred et al., 2019; Niclasen et al., 2012). In this study, the SDQ-Emotional subscale, the SDQ-Total scale, and the SDQ-Impact scale serve as primary outcomes (Hypothesis 1, 2, and 3), while the remaining 4 subscale scores (conduct problems, hyperactivity/inattention, peer relationships problems, and prosocial behavior) are secondary outcomes (Hypothesis 4–7).

The Quality of My Life Questionnaire (QoML; Gong et al., 2007) is used to assess quality of life (QoL). The questionnaire consists of three items: two visual analog scales (VAS) and a categorical measure of change in QoL. The QoML asks “Overall, my life is . . .”. Participants record their responses on a digital VAS for each question stem, which ranges from “the worst” (0) to “the best” (100), with higher scores suggesting better QoL. The questions are only completed by children aged 11 to 17. The QoML serves as a secondary outcome (Hypothesis 8). Previous research established convergent validity in a sample of children living with a chronic health condition (Gong et al., 2007) but the scale has not been validated within a Danish sample.

Physical health is assessed across three domains: somatization, body size perceptions, and sleep quality. Somatization is indicated by one question from the Strength and Difficulties questionnaires, which assesses whether children experience headaches, stomach aches, or nausea (item 3 of the SDQ). This item has previously been used in a national cohort investigation of children's well-being in Denmark (Ottosen et al., 2022). We assessed perceptions of body size, with responses ranging from “much too thin” (1) to “much too fat” (5). This item was drawn from The Health Behaviour in School-aged Children (HBSC) study (Currie et al., 2014), to reflect body image dissatisfaction, a potential predictor of physical and mental health (Currie et al., 2014). Sleep quality is assessed by asking whether the child has had difficulties falling asleep during the last month. This item was also drawn from the HBSC study (Currie et al., 2014, section 5.10). Participants are provided with the following response options: “never” (1), “a couple of times” (2), “almost every week” (3), “more than once a week” (4), and “almost every day” (5). These three items serve separately as secondary outcomes (Hypothesis 9–11). Of note, Denmark is a participating member of the The Health Behaviour in School-aged Children (HBSC) study and thus, the items have been employed in national surveys of school-aged children, aged 11, 13, and 15 years (Madsen et al., 2023).

Participants also respond to questions that tap into key domains targeted by the intervention. These domains concern 1) communicating needs, 2) setting boundaries, and 3) connecting with an adult. Each domain contains three questions developed specifically for this study. The item content for domains 1) communicating needs and 3) connecting with an adult is based on the concepts of instrumental, emotional, and informational support (Taylor, 2011). For the communication needs and setting boundaries domain, the responses are rated on a 4-point scale (e.g., 0 = “No and I haven't needed help”, 1 = “No, even though I have needed help”, 2 = “Yes, one time”, and 3 = “yes, multiple times”). For the connection with an adult domain, responses are rated on a 5-point scale (ranging from 1 = ranging from “very difficult” to 5 = “very easy”). Items for each domain are averaged to create a mean score, and higher scores indicate higher frequency of communication needs, greater frequency of setting boundaries, and lower difficulty in connecting with an adult. For the communicating needs domain, participants report if they have asked for instrumental support (e.g., asked for help with money), emotional support (e.g., told someone that you are upset) and informational support (e.g., asked for advice). For the setting boundaries domain, participants are asked whether they have spoken up if parents have spoken badly about each other, have had a verbal argument in front of them, and if the parents have tried sending each other messages through them. For the connecting with an adult domain, participants are asked how easy or difficult it has been for them to seek instrumental support, emotional support, or informational support. These items were developed specifically for this study by the first and last author, and thus, no psychometric information exists for these items. These three domains serve as secondary outcomes (Hypothesis 12–14).

School non-attendance is measured with one item that examines whether and how many days the child has been absent from school or day care, over the last 4 weeks (for T1 and the T2) or 8 weeks (for T3). Participants respond with the number of days, ranging from 0 to 20 days for T1 and the T2 (i.e., 4-week school- or daycare-period), and 0 to 40 for the T3 (i.e., 8-week school- or daycare-period). Participants are also able to respond that they do not know or that the question is not relevant to them (in cases of vacations or the child not attending school/daycare). The item for school non-attendance follows the construct guidelines proposed by Heyne et al. (2020). A percentage will be calculated for full days of absence, such that higher percentages indicate higher school non-attendance; this variable serves as a secondary outcome (Hypothesis 15).

Degree of conflict is reported by parents and youths (11 to 17 years) using the 6-item self-report Divorce Conflict Scale, developed and validated within a Danish sample (DCS; Hald et al., 2020b). Participants respond to the items using a 4 to 6-point rating scale (response options vary by item stem). Items are summed together to create a score that can range from 0 to 27, such that higher scores indicate greater conflict. This variable serves as an exploratory outcome, as we expect that parents may reduce their conflict in response to 1) exposure to the content of the child intervention and 2) because the child fares better, as child well-being and co-parenting can be a point of conflict for parents (e.g., Johnston, 1994; Hald et al., 2020b).

